**Fig. 1 Fig1:**
[figure not shown]
Study design and patient flow

### Intervention

ZemCAD is based on an existing treatment protocol for patients with chronic depression, developed at the Amsterdam Academic Medical Center [23], adapted for patients with chronic and treatment resistant anxiety or depressive disorders [24]. During thirteen sessions over twenty-six weeks patients and their families are educated about the nature of their chronic disorder, about suicidality and crises, and they learn how to cope with these conditions and events. The trained professional and the patient make an action plan to re-establish social contacts and improve their daily living activities.

ZemCAD consists of three parts. The first part is an introduction phase of three weeks with weekly sessions. The goals for the professionals are to get acquainted with the patient and family, and explain the treatment. Patients make an individual treatment plan, identify symptoms and daily activities, keep a log of symptoms, and learn how they can accept lifestyle changes due to having a chronic disease. The second part is a coaching and treatment phase of fourteen weeks with sessions every second week. Patients start again engaging in social activities, they are stimulated to maintain a daily structure, and learn to use general problem solving skills to cope with their chronic disease. The third part is the final phase of nine weeks with sessions every three weeks. Topics are to make an action plan on how to deal with crisis situations and to further practice with earlier mentioned skills. Finally, patients are referred to primary care. Every primary care practice is asked to select a mental health professional who works in close collaboration with the general practitioner and actively monitors functioning of the patient. After referral to primary care, the general practitioner is responsible for the prescription of medication. Both mental health professional in primary care and general practitioner have easy access to specialized outpatient mental health services for liaison consultation if required.

Patients receiving ZemCAD are allocated to a new and trained professional. This clearly marks the transition from CAU to ZemCAD for both patient and professional. The training of the participating professionals in ZemCAD consists of a two-day course. A prerequisite is that the professionals study the intervention in advance. The two-day course is provided by an expert and trainer in cognitive behavioural therapy and motivational skills for anxiety and depressive disorders. The training combines self-study, lectures, assignments, and group discussions. During the study, three additional booster sessions were given. In addition, in each mental health service monthly booster sessions for the professionals were scheduled.

#### Usual care

Patients who are allocated to CAU continue to receive specialized outpatient mental health care, which usually consists of long-term supportive contacts with a community psychiatric nurse, and pharmacological management by a psychiatrist. In most cases patients continue care with their own community psychiatric nurse. Only if the patient allocated to CAU receives treatment from a community psychiatric nurse who is trained to provide the intervention, the patient needs to switch to a different (untrained) community psychiatric nurse. CAU may also involve termination of treatment in specialized outpatient mental health care and referral to primary care. In the ZemCAD intervention, however, this referral is planned and anticipated within the intervention, while in CAU the referral and termination of the treatment only occurs when indicated.

### Treatment integrity

Patients who are allocated to CAU in most cases continue care with their current community psychiatric nurse. Since there is no clear treatment guideline for CAU, treatment integrity is not assessed in the control group. We do, however, monitor the number of contacts patients have with health care professionals. In the intervention group, treatment integrity is assessed for each participating patient using a checklist that the trained professional completes at the end of each treatment session. In this checklist the trained professional can indicate on which points the treatment differs from the ZemCAD protocol.

### Measurements

At baseline demographics are measured. Measurements take place 6, 12, and 18 months after baseline. Quality of life is measured with the World Health Organization Quality of Life instrument, Brief version (WHOQOL-BREF) [25, 26]. The WHOQOL-BREF measures the overall quality of life in four different areas: physical health, psychological health, social relationships and environment. Anxiety symptoms are measured with the Beck Anxiety Inventory (BAI) [27], a validated self-rated questionnaire to assess the severity of anxiety symptoms. Depression severity is measured with the Patient Health Questionnaire (PHQ-9) [28, 29], a validated self-rated questionnaire to assess the severity of depression symptoms. Empowerment is assessed using the Dutch Empowerment Scale (Nederlandse Empowerment Vragenlijst) [30]. Contacts with health care professionals, medical costs, and productivity costs are measured with the Trimbos and Institute of Medical Technology Assessment questionnaire for costs associated with psychiatric illness (TiC-P) [31]. Using this self-completion questionnaire, direct and indirect costs of health care utilization of patients can be assessed. In addition, the EuroQoL (EQ-5D) [32] is used to compute Quality Adjusted Life Years (QALYs) gained, to be used in the cost-utility analysis.

To get insight in self-management strategies used by patients with chronic and treatment resistant anxiety or depressive disorders, and experiences of patients with a change of care setting, a questionnaire is designed. We do this by organizing focus groups, and use concept mapping [33] for processing the data. The questionnaire is administered during the ZemCAD trial, to all participants, in both conditions. An overview of measurements is provided in Table 1.

**Table 1 Tab1:** Overview of measurements

	Baseline	6 months	12 months	18 months
Demographics	x			
Clinical depression/anxiety (MINI)	x			
Quality of life (WHOQOL-BREF)	x	x	x	x
Anxiety (BAI)	x	x	x	x
Depression (PHQ-9)	x	x	x	x
Empowerment (Dutch Empowerment Scale)	x	x	x	x
Health care costs (TiC-P)	x	x	x	x
Health care costs (EQ-5D)	x	x	x	x
Questionnaire about self-management strategies and experiences with a change of care setting				x

### Data handling

Each participant receives a code. This code is a unique number that is not based on personal information. The list linking participant code and personal information is kept in a separate file stored in a database with access limited to designated researchers and data managers. All our study-related information is stored in secure folders with limited access. Paper-based data collection forms only contain participant codes to maintain participant confidentiality and are stored in a locked cabinet in an area with limited access. Electronic data files are stored on a file system with access restricted to designated researchers and data managers. All results will be described in groups of participants and data will not be traced to a single person. Data will be stored for 5 years after the end of inclusion. The study has low to negligibly risks therefore no data monitoring committee is assigned. Only the designated researchers, or persons assigned by them, will have access to the final data set. Authors of the final manuscript have made substantial contributions to the design, conduction, interpretation and reporting of the trial. We will not use professional writers. Participants, funders and involved professionals will receive a summary of the study results. Final results will be presented via publications and presentations.

### Sample size

The feasibility of our trial is evaluated in a pilot study, which was carried out within one of the participating mental health services. Based on the number of included patients in this pilot and the number of services participating, we expect to be able to include 130–180 patients in our trial. This is enough to detect a standardized mean difference of d ≥ 0.50 in a 2-tailed test at *α* = 0.05 and with a power of (1-β) = 0.80. However, we do not expect such large differences between the conditions on any of the outcomes. With regard to the hypotheses about the clinical effects we assume non-inferiority rather than superiority and with *n* = 130 the non-inferiority margin would be as large as *d* = 0.45 (one sided), which is uninformative. That said, our main hypothesis requires health-economic decision-making. In that context it is more customary to take a probabilistic medical decision-making approach and do not rely on statistical techniques to test hypotheses.

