## Methods/Design

### Design

In a multicenter randomized controlled trial, with randomization at the level of patients in two parallel groups, the protocolized ZemCAD intervention versus care as usual is studied across twelve participating specialized outpatient mental health care services in the Netherlands. Assessments are at baseline, 6, 12 and 18 months and assessors are blind to randomization status.

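### The statement that 130–180 included patients suffice for d ≥ 0.50 at 80% power leaves room, at the lower end of 130, for only two losses over 18 months in an unadjusted comparison

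*Protocol article*

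**What the plan says.** The Sample size section of the protocol article derives the expected number from a feasibility pilot and the number of participating services: "we expect to be able to include 130–180 patients in our trial". The sentence that follows applies to the whole range without qualification: "This is enough to detect a standardized mean difference of d". The smallest difference it names is 0.50, for a two-sided test at the 5% level with 80% power. The number counts patients included. Under Recruitment and randomization, inclusion comes before the baseline questionnaire and before allocation.

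On follow-up, the Design section says: "Assessments are at baseline, 6, 12 and 18 months". Outcomes are collected by questionnaire, and patients may withdraw whenever they wish. The article states no expected loss.

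The Statistical analysis section plans linear mixed-effects models under intention to treat. Baseline variables enter as covariates only if the arms turn out to differ at baseline.

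The Sample size section also limits its own claim. It does not expect differences as large as 0.50 on any outcome, it calls its non-inferiority margin uninformative, and it rests the main hypothesis on health-economic decision-making.

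**The concern.** The power statement is made for patients enrolled, but power depends on patients analysed. At 130 the two can hardly differ before the statement stops being true, and follow-up runs for 18 months on self-completed questionnaires.

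This is more than a detail left to a fuller document. The article makes a positive claim of sufficiency that covers 130, and nothing else in it supports the claim at that end of the range.

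At stake is how the clinical results are read. Quality of life, symptom severity and empowerment are a stated objective, with outcomes expected to be not inferior to usual care. The Sample size section is the article's only statement of how sensitive the trial is on these outcomes. If enrolment ends near 130 with ordinary loss, a null result would be judged against more sensitivity than an unadjusted comparison has.

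**Working it through.** **Inputs from the article.** Total included N = 130 to 180; d = 0.50; two-sided α = 0.05; power 0.80; two parallel groups.

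**Assumptions.** Allocation is 1:1 (blocks of four are stated, a ratio is not). Loss is 0–30% and equal in both arms. The comparison is an unadjusted two-sample t-test.

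**Formula.** With n analysed in total, the noncentrality is δ = d × √(n/4) on n − 2 degrees of freedom. Power is the probability that a noncentral t variable with that δ exceeds the 97.5% point of t (the opposite tail is negligible).

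**Step 1: reproduce the plan's figure.**
- n = 126: 79.5%.
- n = 128: δ = 0.50 × √32 = 2.828, critical value 1.979, power 80.1%.
- n = 130: δ = 0.50 × √32.5 = 2.850, power 80.8%.
- n = 180: 91.6%.

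The stated figure therefore reproduces when nobody is lost, and the requirement is 128 analysed (126 under the normal approximation).

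**Step 2: room for loss.**
- 130 enrolled: 130 − 128 = 2 patients, or 2/130 = 1.5%. The normal approximation allows 4/130 = 3.1%.
- 180 enrolled: 180 − 128 = 52 patients, or 52/180 = 28.9%.

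**Step 3: power under assumed loss, unadjusted.**

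| Enrolled | Loss | Analysed | Power at d = 0.50 | d detectable with 80% power |
|---|---|---|---|---|
| 130 | 0% | 130 | 80.8% | 0.50 |
| 130 | 10% | 117 | 76.5% | 0.52 |
| 130 | 20% | 104 | 71.4% | 0.55 |
| 130 | 30% | 91 | 65.5% | 0.59 |
| 180 | 20% | 144 | 84.6% | 0.47 |
| 180 | 30% | 126 | 79.5% | 0.50 |

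**Step 4: enrolment that leaves 128 analysed.** 128/(1 − loss), rounded up, gives 143 at 10%, 160 at 20% and 183 at 30%. At 20% loss, any enrolment from 130 to 159 falls short of 80% in this comparison.

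**Step 5: effect of always adjusting for baseline.** If the outcome correlates r with its baseline value, the residual SD is √(1 − r²) and the effective standardized difference is 0.50/√(1 − r²). With 104 analysed:
- r = 0.5: 0.50/0.866 = 0.577, power about 83%.
- r = 0.3: 0.50/0.954 = 0.524, power about 75%.

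The article gives no correlation, so both values of r are assumptions.

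**Step 6: the margin in the same section.** With no true difference, n = 130, one-sided 5% and 80% power, the margin is 0.436 (normal) or 0.438 (t), against the stated 0.45. Power at a margin of 0.45 is 81.8%. With 5% loss the margin is 0.447 to 0.450.

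**The case against.** **The arithmetic is correct and the target is not a design driver.** This stands. 128 are needed and 130–180 are expected. The number comes from feasibility, the section says that differences of 0.50 are not expected, and the main hypothesis is not tested statistically. That limits the weight of the point. It does not make the statement true at 130 once a third patient is lost.

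**A complete-case t-test is not the planned analysis.** This stands in part. A mixed model uses patients with partial follow-up, so a patient missing at 18 months still contributes, and some power may be recovered. The article also does not tie the 0.50 claim to a particular time point. But the Sample size section does not rest its claim on the model, and covariate adjustment is conditional on observed imbalance, so the gain in precision is not assured.

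**A condensed article may omit an attrition allowance.** This is fair as far as it goes. The point, however, concerns an unqualified statement that is present in the article.

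**A stronger reading on the margin.** A reader might infer that the 0.45 is also wrong, from "the non-inferiority margin would be as large as" 0.45. The document does not support that. At one-sided 5% and 80% power the value is 0.44, a gap at rounding level and on the conservative side. A clear mismatch (0.49 to 0.50) appears only if one-sided 2.5% is imposed, which the article does not state. The margin is not adopted for the design either.

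**Conclusion.** The point holds in a limited form. At 130 enrolled, the claim of 80% power for d = 0.50 is true in an unadjusted comparison only with at most two losses. At an assumed 20% loss, power is 71.4% and the detectable d is 0.55. The shortfall depends on the loss rate, which the article does not give, on 1:1 allocation, and on making no adjustment for baseline.

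A reader might go further and conclude that the trial cannot deliver the stated power under any realistic follow-up. The figures contradict that: 180 enrolled with 20% loss gives 84.6%, and 130 enrolled with 20% loss gives about 83% if every model adjusts for a baseline score correlated 0.5 with the outcome. A further deduction for clustering by professional would rest on an intraclass correlation and a caseload that the article does not give, so none is made.

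Severity is low.

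**What to change.** Change one of two texts in the protocol article or the underlying protocol.

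1. **Restate the claim for analysed patients** under a named loss assumption in the Sample size section. For example: *With 130 enrolled and 20% loss (104 analysed), an unadjusted comparison has 71% power for d = 0.50 and 80% power for d = 0.55; with 180 enrolled and the same loss, power for d = 0.50 is 85%.* The sponsor should put in the loss rate it expects, from the pilot if that is informative.
2. **Or keep d = 0.50 and support it.** In the Statistical analysis section, replace the rule that adjusts only when baseline differences appear with adjustment for the baseline value of each outcome in every model, and state the assumed correlation. At 20% loss, 0.5 supports the claim (about 83%); 0.3 does not (about 75%).

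Neither option adds patients or measurements, because the baseline scores are already collected. The cost of the first is a slightly less favourable statement of sensitivity. The cost of the second is a fixed covariate in place of a conditional one. If the section is being edited anyway, giving the one-sided alpha and the power beside the margin would save readers from guessing them.

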### Statistical analysis

Descriptive statistics are used for presenting the demographics of the sample. All outcome analyses are conducted in agreement with the intention-to-treat (ITT) principle, as required by the CONSORT statement [34]. To that end, we use linear mixed-effects models. If differences in baseline data are present, we adjust for relevant baseline characteristics, by including baseline variables as covariates in the model. To see how effects develop over time we also model interactions of the treatment with time in the linear mixed-effects models. All analyses are conducted in SPSS 22 and Stata 13.1 or later versions.

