### Recruitment and randomization

Patients that are eligible for participating in the ZemCAD study according to the inclusion and exclusion criteria are asked to participate by their community psychiatric nurse. This nurse informs the patient about the study and provides an information letter to take home. If the patient is interested and consents to participate, the signed informed consent is sent to the coordinating research centre. To check the inclusion and exclusion criteria formally, the current DSM-IV disorders present in the patient were diagnosed with the Mini-International Neuropsychiatric Interview (MINI interview) in the mental health service that provides the treatment of the patient. The MINI is a well-validated semi-structured diagnostic interview used to establish psychiatric disorders according to the DSM-IV [22]. After inclusion, patients receive the baseline questionnaire. Patients and community psychiatric nurses are blind to the patient’s condition until they have completed the baseline questionnaire. Then the patient is allocated to ZemCAD or CAU, using a randomization schedule designed by an independent statistician. To evenly distribute ZemCAD/CAU across community psychiatric nurses, block randomization (block size of four) of patients is used. Questionnaires are completed over the internet. If a patient has no access to the internet, the questionnaires are completed on paper. Patients are informed that participation in the study is voluntary and that they can withdraw from the study at any time. An overview of the study design and patient flow is provided in Fig. 1.

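### Baseline adjustment depends on observed imbalance, so the data choose the covariates and efficient use of each clinical outcome's baseline value is not guaranteed

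*Protocol article*

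**What the plan says.** The protocol article's Statistical analysis section commits the outcome analyses to intention to treat and then names the method: "To that end, we use linear mixed-effects models". The adjustment rule follows: "If differences in baseline data are present, we adjust for relevant baseline characteristics, by including baseline variables as covariates in the model". For the course of effects over time, "we also model interactions of the treatment with time in the linear mixed-effects models". The section gives no criterion for a difference and no list of relevant characteristics. It does not say whether the baseline measurement is a covariate, a response at the first time point, or a response with equal means imposed on the two arms.

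The data for adjustment exist. Under Design, "Assessments are at baseline, 6, 12 and 18 months". Table 1 under Measurements marks WHOQOL-BREF, BAI, PHQ-9 and the Dutch Empowerment Scale at all four times, and the TiC-P and EQ-5D as well. The one instrument without a baseline value is the "Questionnaire about self-management strategies and experiences with a change of care setting", given at 18 months only and serving the descriptive objectives. Under Recruitment and randomization, "Patients and community psychiatric nurses are blind to the patient’s condition until they have completed the baseline questionnaire", and allocation comes after that.

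**The concern.** The rule ties adjustment to the wrong property. With random allocation, a baseline difference between arms says nothing about whether a variable is worth adjusting for. What matters is how strongly the variable predicts the outcome, and the baseline score on the same instrument is usually the best predictor available. A rule triggered by imbalance has two consequences.

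- The model is settled only after the baseline data have been compared by arm, and someone must then judge which differences count and which variables are relevant.
- Depending on how the mixed model is set up, a prognostic baseline value may be left out, or used inefficiently, whenever the arms happen to look alike.

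Precision is scarce here. The Sample size section says "we expect to be able to include 130–180 patients in our trial", and it calls the non-inferiority margin attainable at the lower figure (d = 0.45) uninformative. The Background states a non-inferiority expectation for quality of life, symptoms and empowerment, so wider intervals bear directly on those outcomes.

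**Working it through.** **Inputs from the article.** N = 130 (lower end of 130-180), d = 0.50, two-sided alpha 0.05, power 0.80, non-inferiority margin d = 0.45 at n = 130 (one-sided, level not stated). **Assumptions.** Equal allocation, 65 per arm; r between 0.3 and 0.7; a p-value trigger for the adjustment rule. None of these is in the documents.

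**1. The plan's own figures.** Per arm, n = 2(1.96 + 0.8416)² / 0.50² = 62.8, so 63, or 126 in total. The t-test version needs 64 per arm, 128 in total (power 0.801). At 65 per arm, power is 0.813 (normal) or 0.808 (t). The claim for 130 patients is reproduced, using an unadjusted comparison. The margin detectable with 80% power at n = 130 is (1.645 + 0.8416) × √(4/130) = 0.436 at one-sided 0.05 and 0.491 at one-sided 0.025; the stated 0.45 is close to the first.

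**2. Standard error under each handling of baseline.** This is for one follow-up with complete data, relative to the unadjusted SE of √(4/130) = 0.175:

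- always adjusted for baseline (ANCOVA): √(1 − r²)
- baseline as an unconstrained response, which gives a change-score contrast: √(2(1 − r))
- ratio of the first to the second: √((1 + r)/2)

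| r | ANCOVA | SE reduction vs unadjusted | Change score | SE reduction, ANCOVA vs change score |
|---|---|---|---|---|
| 0.3 | 0.954 | 5% | 1.183 | 19% |
| 0.5 | 0.866 | 13% | 1.000 | 13% |
| 0.6 | 0.800 | 20% | 0.894 | 11% |
| 0.7 | 0.714 | 29% | 0.775 | 8% |

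With baseline as a response and its means constrained equal, there is no precision loss relative to ANCOVA.

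**3. In terms of the margin.** Multiplying 0.436 by the ANCOVA factor gives 0.416, 0.378, 0.349 and 0.311 for r = 0.3, 0.5, 0.6 and 0.7. With the change-score factor at r = 0.5, 0.6 and 0.7 it is 0.436, 0.390 and 0.338.

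**4. The conditional rule itself.** This was simulated with 65 per arm, one follow-up and 40,000 runs per setting. Baseline was a covariate only if its between-arm test fell below the trigger.

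| r | Trigger | Type I error | Power at d = 0.50: rule | Power: always adjusted | SD of estimate: rule | SD: always adjusted |
|---|---|---|---|---|---|---|
| 0.5 | 0.05 | 0.043 | 0.818 | 0.903 | 0.169 | 0.152 |
| 0.6 | 0.05 | 0.040 | 0.824 | 0.940 | 0.167 | 0.141 |
| 0.7 | 0.05 | 0.036 | 0.829 | 0.976 | 0.163 | 0.126 |
| 0.5 | 0.20 | 0.038 | 0.838 | 0.901 | 0.161 | 0.152 |
| 0.6 | 0.20 | 0.034 | 0.854 | 0.941 | 0.154 | 0.141 |
| 0.7 | 0.20 | 0.027 | 0.868 | 0.977 | 0.145 | 0.126 |

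Never adjusting gives power of about 0.81. With the 0.05 trigger the rule therefore recovers little of the available precision. Its error rate lies below 5% and moves with a threshold the article does not give. Selection among several candidate covariates was not simulated.

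**The case against.** The strongest reply is that the simulated rule may not be the planned model. The article plans linear mixed models with treatment-by-time terms, and baseline is one of its four assessment times. A natural reading is that baseline is already in the model as a response, with the conditional sentence reaching only other patient characteristics. A reader might infer that the outcome's baseline value is dropped in most realisations; the text does not establish that. On the response reading, the SE reduction for r of 0.5 to 0.7 is 8-13%, and with equal baseline means it is nil.

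A reader might also infer a loss of up to half the effective sample size, or power of 63-64% against 74-89%. Those figures need baseline to be absent as a response, r of 0.5 to 0.7 and, for the power figures, a true d of 0.40 and a p < 0.05 trigger. None of this is in the documents. At the article's own d = 0.50, the simulated rule still exceeds 80% power.

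A third inference, inflated false positives, is contradicted by the simulation, which is conservative.

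Reach is also limited. The main hypothesis is health-economic and rests on bootstrapping, and the article does not clearly apply the adjustment rule there.

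Finally, the trigger, the covariate list and the coding of baseline may properly sit in an analysis plan that is not shown. Their absence is no fault. What stands is the stated principle that adjustment follows observed differences. Unless baseline means are constrained equal, which the article does not say, precision is given up; and on any reading, covariates may be chosen after the data are seen.

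**Conclusion.** The point holds for the clinical outcome models. The rule makes the covariate set depend on chance imbalance and leaves efficient use of the pre-allocation baseline values unsecured.

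Its size is conditional on two unknowns: r, and the place of baseline in the mixed model. For r of 0.5 to 0.7, always adjusting cuts the SE by about 13-29% relative to no adjustment if baseline is only a conditional covariate. That is equivalent to 1/(1 − r²) = 1.3 to 2.0 times the sample size. It cuts the SE by about 8-13% if baseline is an unconstrained response, equivalent to 2/(1 + r) = 1.2 to 1.3 times. With equal baseline means there is no precision loss. At r = 0.3 the gain over no adjustment is about 5%.

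The documents do not support a claim of inflated type I error, of a fixed large power loss, or of damage to the economic evaluation. It is a worthwhile improvement to a stated rule, and does not by itself invalidate the analysis.

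**What to change.** Replace the conditional sentence in the Statistical analysis section with:

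> Each clinical outcome model includes the baseline value of that outcome in all cases, whatever the observed balance (or baseline enters as a first time point with means constrained equal in both arms); no covariate is selected from observed baseline differences.

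The authors should choose one of the two forms before the outcome data are compared by arm. The change costs one sentence and uses data already scheduled in Table 1. It needs no additional patients or visits. The point gives no reason to require mental health service as a covariate.
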